## Abstract

**Background:**

Coronary artery disease (CAD) is among the main causes of hospitalization and death worldwide, therefore, the implementation of programs to reduce its impact is necessary. Supervised cardiac rehabilitation has been shown to have positive effects on CAD control. However, there are barriers to patient participation in the traditional, face-to-face cardiac rehabilitation programs, mainly in low-resource environments.

**Objective:**

This study aimed to verify patient compliance to a home-based cardiac rehabilitation program, which includes unsupervised health education and physical exercises, guided by telephone. Moreover, we compare this new method to the traditional supervised cardiac rehabilitation offered in most hospital centers.

**Methods:**

We present here a two-arm, single-blinded, and randomized controlled design protocol, which compares the traditional cardiac rehabilitation (CenterRehab) with the home-based cardiac rehabilitation (Home-Based) in 72 patients affected by CAD. The primary outcome is the compliance to the cardiac rehabilitation sessions. The secondary outcomes (to evaluate effectiveness) include measurable variables such as functional capacity, CAD risk factors (blood pressure, waist circumference, glycemic, cholesterol levels, depressive symptoms, and the level of physical activity), the patient’s quality of life, the disease knowledge, and the morbidity rate. Parameters such as the program cost and the usability will also be evaluated. The programs will last 12 weeks, with a total of 60 rehabilitation and 6 educational sessions. Patients of the CenterRehab program will participate in 24 supervised sessions and 36 home sessions, while the patients of the Home-Based program will participate in 2 supervised sessions and 58 home sessions, guided by telephone. After the 12-week period all participants will be recommended to continue practicing physical exercises at home or at a community center, and they will be invited for re-evaluation after 3 months. The outcomes will be evaluated at baseline, and after 3 and 6 months.

**Results:**

Participants are currently being recruited for the trial. Data collection is anticipated to be completed by October 2019.

**Conclusions:**

This is the first study in Brazil comparing the traditional cardiac rehabilitation approach with a novel, home-based protocol that uses an accessible and low-cost technology. If positive results are obtained, the study will contribute to establish a new and viable model of cardiac rehabilitation.

**Trial Registration:**

ClinicalTrials.gov NCT03605992; https://clinicaltrials.gov/ct2/show/NCT03605992

**International Registered Report Identifier (IRRID):**

DERR1-10.2196/13901

## Introduction

### Background

Cardiovascular diseases (CVDs), including its main form, the coronary artery disease (CAD), are the leading cause of death worldwide [1]. CAD has a negative impact on morbidity, quality of life, and survival of the population [2]. In Brazil, CAD is among the main causes of hospitalization and death [3]; thus, the implementation of programs that minimize these impacts is necessary [4-6].

The World Health Organization defined cardiac rehabilitation (CR) as a set of activities and interventions necessary to ensure the best physical, mental, and social conditions for the patients with chronic or postacute CVD, to be able to preserve or return to their appropriate place in the society by their own efforts [7]. The main goal of CR is the education and training for self-care, with an emphasis on physical exercise, as its positive effects on improving the quality of life as well as reducing hospitalization and the risk of death in CAD patients have been thoroughly demonstrated [8-10].

Despite the benefits of supervised CR programs, such interventions have been shown to be impractical in low- and middle-income countries (LMICs). Only 40% of them currently have a CR program, and in those, there is a grossly insufficient capacity [11]. In Brazil, it is estimated that more than 3.9 million people would benefit from a CR program; however, less than 20% of them have access to it [12]. The main obstacles for participation in CR programs in low-resource environments are the accessibility to programs provided by the public health system and the lack of time because of professional and family commitments and transport availability [10,12]. Therefore, alternative CR models are necessary to improve participation, considering the community diversities and the economic viability [13,14].

Therefore, the home CR model presents some advantages and improves patients’ participation and compliance to a healthy lifestyle and drug treatment as well as facilitates the patient and health professional education process [15,16].

Home-based CR is a term used to refer to CR at home or in other nonclinical settings, such as community centers, health clubs, and parks. This term also encompasses the use of information and communication technologies and hybrid form rehabilitation (ie, some sessions held in person at the rehabilitation clinic in conjunction with rehabilitation sessions at home) [16]. The home-based CR approach has been shown to be more efficient compared with conventional rehabilitation programs [16-19]. Studies showed that CR programs performed at home can overcome the traditional participation barriers and promote effects comparable with CR outpatients regarding the mortality, risk of recurrent coronary event, cardiovascular risk factors, and exercise capacity [17-19].

Different models of interventions and cardiac monitoring are used in home rehabilitation programs [5,6,15,17,19]. However, most models use equipment demanding a higher technological ability from the participants, such as manipulating digital equipment, downloading data from an exercise tracking equipment to a computer, using a chat software, and receiving information via email. Patients with a low education level living in a low-resource environment could have difficulties in making proper use of the required equipment. Thus, one of the challenges in designing a home-based CR program in LMICs is the use of a feasible, accessible, and viable technology for monitoring patients. Ideally, the technology should ensure an ideal heart rate range to allow for the expected training effects, without increasing the risk of adverse effects.

### Objectives

The aim of this trial is to verify the compliance and the effectiveness of a home-based CR program, which includes the health education and physical exercises components, mostly unsupervised and guided by telephone. We also compare this novel approach with the traditional, supervised CR program offered in most Brazilian hospital centers.

## Methods

### Study Design and Procedure

The study is a single-blind, randomized controlled trial. The researchers will be blinded for the treatment’s allocation during the duration of the trial. Owing to the nature of the intervention, neither the participants nor the program staff can be blinded to the allocation type. Patients will be recruited at the outpatient University Hospital's CR Center. The study will conform to the Consolidated Standards of Reporting Trials (CONSORT) guidelines for nonpharmacological interventions [20]. After being invited to participate in the study, the volunteers will sign a consent form and will be randomized into 2 different groups: traditional CR (mostly supervised) and home-based CR (mostly unsupervised). The randomization will be made in blocks of 4 volunteers at a time [21]. A blinded researcher will evaluate the participants before and after the intervention and will collect the data into a database.

This study protocol is in accordance with the most recent version of the World Medical Association Declaration of Helsinki. This study was approved by the Ethics Committee in Research of the Universidade Federal de Minas Gerais, Brazil and was registered under the CAAE 51528615.3.0000.5149, on February 23, 2016. The CONSORT flowchart is reported in Figure 1.

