### Participants

Patients will be eligible if they meet the following inclusion criteria: (1) if they have a CAD and have undergone angioplasty or myocardial revascularization surgery and (2) if they had a heart attack, provided that they were considered at low and moderate risk for the practice of physical exercise of moderate intensity, according to the stratification for the risk of events during a cardiovascular rehabilitation program [23]. Moreover, the inclusion criteria would require that patients have clinical stability (according to a medical evaluation) and be resident of the Belo Horizonte metropolitan region. Participants will be excluded if the history of recent cardiac events or clinical decompensation is more recent than 1 month and if at least one of the following limitations is present: peripheral arterial occlusive disease, preventing the test of maximum exercise level (emergence of claudication before the maximal cardiorespiratory fatigue); chronic pulmonary disease (ie, chronic obstructive pulmonary disease, pulmonary fibrosis, and pulmonary arterial hypertension of precapillary etiology); history of ventricular fibrillation or sustained ventricular tachycardia in the last year; and physical, cognitive, and/or social limitations that prevent participation in a physical exercise program and the comprehension of monitoring the device usage.

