#### Primary Outcome: Compliance of Cardiac Rehabilitation Sessions

The primary outcome of this trial was carefully chosen. A correct exercise compliance promotes positive changes in behavior and lifestyle [18], besides reducing the risk for rehospitalization and improving quality of life [26].

The compliance on CR sessions will be analyzed by the percentage of participants who completed at least 75% (45/60) of the sessions. This parameter will be evaluated after 3 months.

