### Sample Size

On the basis of previous CR studies [34] and on our 7-year experience in providing rehabilitation services in a university hospital, we estimated a compliance of 70% in the control group and of 96% in the home-based group. We calculated that for an alpha significance level of 5% and a power of 80% in the Fisher exact *t* test, the sample size of each group should be at least 36 volunteers. We also calculated the sample size for the secondary outcome, the functional capacity (ISWT), considering an arbitrary small size effect of 0.25. To detect a statistically significant difference within and between groups (2×2), at least 34 volunteers in each group are needed, keeping the same values of alpha and power. After a pilot study with 10 subjects in each group, the sample calculation will be performed again. All the calculations were made using the G Power 3.1.9.2. software (Franz, Universitat Kiel) [35].

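### A single block size of 4 at one centre with unblinded programme staff makes a third of allocations predictable to anyone who tracks them, an opportunity for selection bias in a behavioural primary outcome

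*Protocol article*

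**What the plan says.** All of the following is in the Protocol article.

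- **Block size** (Study Design and Procedure): "The randomization will be made in blocks of 4 volunteers at a time". One size is given, with no variation and no stratification.
- **Setting** (same section): "Patients will be recruited at the outpatient University Hospital's CR Center". This is a single centre.
- **Blinding** (same section): "neither the participants nor the program staff can be blinded to the allocation type". The section also says "The researchers will be blinded for the treatment’s allocation during the duration of the trial", and it assigns the evaluations to a blinded researcher.
- **Sequence** (same section): after invitation, "the volunteers will sign a consent form and will be randomized into 2 different groups".
- **Eligibility** (Participants): the criteria include clinical stability on medical evaluation, and they exclude "physical, cognitive, and/or social limitations that prevent participation in a physical exercise program".
- **Primary outcome** (its own section): "the percentage of participants who completed at least 75% (45/60) of the sessions", assessed at 3 months.
- **Size** (Sample Size): "we estimated a compliance of 70% in the control group and of 96% in the home-based group", leading to 36 per group, 72 in all.
- **Accrual** (Results): 51 patients had consented between February 2018 and August 2019, and all 51 had been evaluated at 3 months. Recruitment was due to end in October 2019.

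**The concern.** When the block size is small and constant and earlier allocations are visible, the later places in each block can be worked out before the next patient is enrolled. Here the programme staff see every allocation, at the centre where patients are recruited, and accrual is slow: 51 patients in about 19 months is fewer than 3 a month, so keeping count is easy.

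The primary outcome is attendance and completion of sessions. A person who meets a candidate may form a view on whether that patient will reach 45 of 60, and some eligibility criteria leave room for judgement. If such a person also knew the next arm, inviting one patient now and another later would shift the comparison of compliance between the arms. Blinded evaluation at 3 months does not protect against this, because the selection would happen before enrolment. No analysis can reliably remove it afterwards.

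**Working it through.** **1. The plan's own figure.** Inputs from Sample Size: 70% against 96%, alpha 5%, power 80%, Fisher exact test. The exact power of the two-sided test, summed over both binomial distributions, is 0.796 with 35 per group and 0.813 with 36. The stated 36 per group reproduces, and nothing below changes it.

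**2. Share of determined allocations.** A 1:1 block of 4 has 6 possible orders: AABB, ABAB, ABBA, BAAB, BABA, BBAA.
- The 4th place is always forced: 6 of 6.
- The 3rd place is forced when the first two match (AABB, BBAA): 2 of 6.
- Forced places per block: 1 + 2/6 = 4/3. Share: (4/3)/4 = 1/3.
- Over 72 patients (18 blocks): 18 × 4/3 = 24.

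Always guessing the arm that lags is right for 17/24 = 70.8% of all places.

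**3. Allocations still to come.** If the 51 patients were allocated in sequence, 51 = 12 × 4 + 3.
- Already made: 12 × 4/3 + 1/3 = 16.3 expected forced places.
- Remaining: 24 − 16.3 = 7.7 of 21. As a check, number 52 is the 4th place of block 13 and is forced, and five further blocks add 5 × 4/3 = 6.7, so 1 + 6.7 = 7.7.

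**4. Possible size of a bias.** The document gives no figure for how strongly a recruiter could select, so this is an assumption shown over a range. Suppose there is no true effect, and on forced places only the chance of compliance is shifted by +d when one arm is next and −d when the other is. The spurious difference is about (1/3) × 2d. The rejection rates come from 20,000 simulated trials of 18 blocks per setting, with the two-sided Fisher test at 5%; the two values are for base compliance of 70% and 83%.

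| Shift d (points) | Spurious difference (points) | Rejection rate, base 70% / 83% |
|---|---|---|
| 0 | 0 | 0.029 / 0.025 |
| ±5 | 3.3 | 0.035 / 0.034 |
| ±10 | 6.7 | 0.058 / 0.067 |
| ±15 | 10 | 0.101 / 0.128 |

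The Fisher test is conservative at this size, so a modest shift stays below the nominal 5%. For example, a 15-point gap between the arms confined to the forced third gives 15/3 = 5 points; the exact rejection rate at 80% against 85% with 36 per group is 4.8%, compared with 2.2% at 85% in both arms.

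**The case against.** The strongest objection is that predictability needs a person who both knows the block size and sees the earlier allocations, and who also decides whom to enrol. The article does not identify such a person. Recruitment at the centre is not the same as recruitment by the treating staff, and the article says the researchers are blinded to allocation. A condensed article commonly leaves concealment details to the full protocol, so its silence on them is not a fault. This stands, and it limits the point to an opportunity. It does not remove the point, because the single small block size is something the article does fix, and the people who know the allocations work where patients are recruited.

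A second objection is that four volunteers at a time could mean four consented patients randomised together, which would rule out selection within a block. The wording allows this, but the accrual fits it poorly: all 51 patients had been evaluated at 3 months, so presumably all had been allocated, and 51 is not a multiple of 4.

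Third, the article's publication cannot have revealed the block size to those who enrolled the 51 patients it reports. That is correct.

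Two stronger readings are tempting and are not supported:
- A reader might infer that the baseline evaluation follows randomisation. That rests only on the order of sentences. The article says evaluation takes place before and after the intervention, and the flow chart is not shown in the text available here.
- A reader might infer that mild selection would produce too many false positive results. The 4.8% above is still under the nominal 5%; an excess appears only with stronger shifts, about ±10 points or more in the table.

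**Conclusion.** The point holds as a design weakness of moderate importance. For someone who knows the block size and the earlier allocations, one third of allocations are determined in advance: 24 of 72 expected, and about 7.7 of the remaining 21. This rests on three readings: that 4 is the only block size, that allocation is 1:1 (36 per group), and that patients are allocated one after another.

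The document does not show that selection took place, that recruiters knew the block size, or that they were the unblinded staff. The size of any bias depends wholly on assumed selection. A correction now would reach only the allocations not yet made, about 21 if the trial continues to 72.

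**What to change.** For the remaining allocations, replace the fixed blocks of 4 with randomly varying block sizes, for example 2, 4 and 6, not disclosed to recruiting staff, on a list generated and held outside the programme. If recruiters have been kept unaware of the block size and the earlier allocations throughout, a sentence saying so would answer most of the point.

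**What it gains.** With an equal mix of 2, 4 and 6, even a person who knew which sizes are used would be certain of few allocations. Certainty arises only in a block of 6 whose running count does not return to balance before its end: AAABBB (3 forced places), AABABB (2) and their mirror images. That is 10/20 = 0.5 place per block of 6, or 0.5/12 = 4.2% of places, against 33.3% now.

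**What it does not gain.** Guessing the lagging arm still succeeds in (2 × 0.75 + 4 × 0.708 + 6 × 0.683)/12 = 70.3% of places, against 70.8% now. Varying the sizes removes most of the certainty but not the informed guess, so keeping the list and the running count away from whoever enrols matters as much as the sizes.

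**Cost.** A new list, and a possible final imbalance of one to three patients if recruitment stops inside a block. If the new list starts at number 52, the one-patient imbalance left by the incomplete 13th block could add to this. The sample size and the primary test do not change.

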**Figure 1 figure1:**
[figure not shown]
Consolidated Standards of Reporting Trials flow chart. CR: cardiac rehabilitation.

### Patient and Public Involvement

Patients and the public were not directly involved in the study design. The intervention design was chosen based on previous studies, which reported that home-based CR programs promoted comparable effects with CR outpatient regarding the mortality, recurrent coronary event risk, cardiovascular risk factors, and exercise capacity [2,16-19,22]. The results of the study will be disseminated through institutional media, and educational activities will be conducted with CR patients and the study participants.

### Participants

Patients will be eligible if they meet the following inclusion criteria: (1) if they have a CAD and have undergone angioplasty or myocardial revascularization surgery and (2) if they had a heart attack, provided that they were considered at low and moderate risk for the practice of physical exercise of moderate intensity, according to the stratification for the risk of events during a cardiovascular rehabilitation program [23]. Moreover, the inclusion criteria would require that patients have clinical stability (according to a medical evaluation) and be resident of the Belo Horizonte metropolitan region. Participants will be excluded if the history of recent cardiac events or clinical decompensation is more recent than 1 month and if at least one of the following limitations is present: peripheral arterial occlusive disease, preventing the test of maximum exercise level (emergence of claudication before the maximal cardiorespiratory fatigue); chronic pulmonary disease (ie, chronic obstructive pulmonary disease, pulmonary fibrosis, and pulmonary arterial hypertension of precapillary etiology); history of ventricular fibrillation or sustained ventricular tachycardia in the last year; and physical, cognitive, and/or social limitations that prevent participation in a physical exercise program and the comprehension of monitoring the device usage.

### Intervention

The parameters for monitoring the exercise prescription compliance will be the same for both groups. An exercise session will be constituted by 5 to 10 min of warm up, 40 min of aerobic activity with a heart rate between 60% and 80% of the heart’s maximum rate, and 5 to 10 min of cool down [24]. The educational sessions will be given to both groups in 6 meetings of 40 min, using a systematized protocol [25]. In these meetings, topics regarding the control of risk factors and the treatment of CVDs will be taught. After the 12 weeks of intervention, all participants will be encouraged to continue practicing physical exercises either at home or at the community center and will be invited for a re-evaluation after 3 months.

### Groups

#### Traditional and Face-to-Face Cardiac Rehabilitation as Control Group

The control group will receive, in person, the usual program consisting of supervised exercises and health educational activities at the CR center. This intervention will last for 12 weeks, with a total of 60 sessions: 24 supervised and 36 home sessions (5 exercise sessions per week). The participants of this group will be instructed to complete a training diary, with information regarding the frequency and intensity of exercises (using a scale of perceived exertion) as well as the presence of symptoms during or after exercises. The same information will be registered in their individual file while exercising at the CR center.

#### Home-Based Cardiac Rehabilitation

The participants of this program will perform their exercise mostly at home. Weekly phone calls will be programmed to check the correct execution of the previous stage of the program and also identify and register the presence of symptoms and undesirable effects. Monthly meetings will be programmed for educational activities to verify if the exercises and training diary are being both performed and compiled correctly and to address any kind of issue by the participants.

This intervention will have a duration of 12 weeks, with a total of 60 sessions: 2 supervised sessions and 58 home sessions (5 exercise sessions per week).

During the first week, all individuals of the home-based group will be receiving training regarding the utilization of the monitoring equipment. A heart rate monitor with the heart rate zone individually calculated will be given to each participant at the first supervised session. Furthermore, all participants of this group will be using a step counter (pedometer) to monitor the number of prescribed exercises as well as an aid to compile the training diary with information regarding the frequency of exercises, the presence of symptoms during the exercise, the perceived exertion, and the number of daily steps.

